### Sample Size

The average breast reconstruction patient attends two in-person follow-up visits within the first month after surgery. If we assume that we can avert at least one in-person visit in the mobile app arm and that we have equal number of participants in both groups, we can use the E-test for count data to generate a sample size of 64 (32 patients per group) at a power of 95% (*P*=.05). The E-test is more robust and more powerful than the Conditional test (C-test) originally described to compare two counts. If we assume a 10% dropout rate, we will increase our sample size target to 36 patients per group.

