#### Secondary Outcomes

The total number of health care telephone calls and emails (including specialist, family physician, and emergency department) related to the surgery will be captured at 4 weeks after surgery by the study coordinator over telephone (see Multimedia Appendix 3).

All complications will be recorded including infection, seroma, hematoma, and wound dehiscence. Among patients who receive tissue expanders, deflation is another possible complication. These complications will be collected via telephone survey at 4 weeks postoperative (see Multimedia Appendix 3).

Both mobile app and conventional follow-up patients at 4 weeks postoperative will complete our cost survey (Multimedia Appendix 4). The survey will collect data necessary to conduct cost estimates (presence of caregiver at time of follow-up, overnight hotel stays prior to clinic visit, etc).

For the purposes of this study, patients will receive a managed (loaner) mobile phone; however, a bring-your-own-device model is a more scalable solution and will be represented in the cost-effectiveness data [25].

In-person follow-up costs include foregone leisure time or income for the patient and foregone income for the caregiver, travel, and overnight hotel stay and parking costs associated with follow-up visits. Our cost survey (Multimedia Appendix 4) will collect information on caregiver presence at appointments, overnight hotel stays prior to appointments, total time commitment of in-person follow-up, and return to work information. In the literature, leisure time is often valued more than foregone income because subjects are choosing to forego their income for that leisure time. We will equally weight foregone income and leisure time, as patients are not choosing to be off work. They are off work because of a medical condition. We will determine foregone income based on average Ontario wages for a given age and sex of the patient. We will determine travel costs based on distance from home postal code to WCH.

Mobile phone follow-up costs include the foregone leisure time to submit follow-up data and the cost of data submission. We will determine foregone leisure time based on questionnaire time stamps from software records. Patient training sessions are held while patients are waiting for their preoperative appointment. There are no additional patient costs associated with this time.

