### Measuring Predictor Variables

Age impacts foregone wage estimates, and postal code impacts travel cost estimates. The type of surgical procedure, ASA classification, BMI, and preoperative radiation impacts rates of successful surgery at 30 days postoperative. Therefore, these variables are considered potential predictors of cost-effectiveness.

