### Net Benefit Regression

We will perform a person-level net benefit regression to determine the cost-effectiveness of this intervention. We will define cost as all societal costs incurred over the 30 days after surgery. We will define effect as the rate of complication over the 30 days after surgery. We will regress net benefit (dependent variable) on study arm, age, distance from home to hospital (km), BMI, BMI^2^, ASA classification, radiation status, and major or minor procedure (independent variables). Net benefit, age, distance, BMI, and BMI^2^ are continuous variables. ASA classification is a categorical variable. Study arm, radiation status, and major or minor procedure are binary variables (1=mobile app; 0=in-person and 1=yes, 0=no), where:

nb = B0 + B1(TX) + B2(age) + B3(km) + B4(BMI) + B5(BMI^2^) + B6(ASA) + B7(radiation) + B8(major/minor)

We will perform regression diagnostics and use these diagnostics to advise on the use of parametric versus non-parametric generation of 95% confidence intervals. We will use our net benefit regression to generate an incremental net benefit (INB):

INB = WTP * (effect_i_ – effect_c_) – (cost_i_ – cost_c_), where:

effect_i_ = mean effect of the intervention, ie, rate of complication in the mobile app arm at 30 days

effect_c_ = mean effect of the control, ie, rate of complication in the in-person arm at 30 days

cost_i_ = mean cost of the intervention, ie, societal costs from baseline to 30 days

cost_c_ = mean cost of the control, ie, societal costs from baseline to 30 days

In this situation, where willingness to pay is unknown, we assigned numerous values for willingness to pay and generated a cost-effectiveness acceptability curve (CEAC) based on these theoretical values [26]. The CEAC illustrates the probability that the intervention is cost-effective by graphing the probability that B1>0 as a function of willingness to pay (WTP) [27].

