## Discussion

### Relevance

At Women’s College Hospital, over 5000 elective ambulatory surgeries are performed each year. These numbers are small compared to other hospitals, such as the nearby Trillium Health Center, where over 20,000 surgeries are performed annually. These numbers will continue to grow as we follow trends in the United States where currently 60-70% of the surgical procedures are performed in the ambulatory setting [28]. Smartphones are becoming ubiquitous throughout Ontario. Using such an ubiquitous technological platform to reduce health care costs for patients and providers in an already large and growing patient population is in concordance with the Ontario Action Plan. Telemedicine is identified as a way to improve access to specialty care among underserviced communities [29]. Breast reconstruction is an underused option for patients, despite its well-known psychosocial benefits in breast cancer patients [2,8]. In fact, Canada underperforms next to countries like England and the United States. Particularly, low income and nonurban residence is associated with decreased rates of breast reconstruction [9]. By reducing costs to society, of which a component represents costs borne by patients, and eliminating the barriers of distance, telemedicine can improve access to breast reconstruction among breast cancer survivors.

Telemedicine literature is often criticized for its lack of rigorous economic evaluation [28]. In assessing the cost-effectiveness of mobile phone follow-up, we will determine general parameters that are necessary to make a telemedicine postoperative follow-up program more cost-effective. Upcoming telemedicine pilot programs can model costs around these general parameters.

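### The net benefit model has main effects only, so its covariates, distance in particular, cannot be read as predictors of the app's cost-effectiveness

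*Protocol article*

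**What the plan says.** Methods, Measuring Predictor Variables, explains that age drives wage estimates, postal code drives travel cost, and procedure, ASA class, BMI and radiation affect surgical success. It concludes: "Therefore, these variables are considered potential predictors of cost-effectiveness".

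Results, Net Benefit Regression, puts these variables into a model written out in full: "nb = B0 + B1(TX) + B2(age) + B3(km) + B4(BMI) + B5(BMI^2^) + B6(ASA) + B7(radiation) + B8(major/minor". There is no product term. Cost-effectiveness is read from one coefficient, by "graphing the probability that B1>0 as a function of willingness to pay (WTP". On cost it says: "We will define cost as all societal costs incurred over the 30 days after surgery".

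Measuring Outcome Variables, Secondary Outcomes, ties distance to cost: "We will determine travel costs based on distance from home postal code to WCH". Sample Size supplies the expected visit numbers: "The average breast reconstruction patient attends two in-person follow-up visits within the first month after surgery", with at least one assumed averted in the app arm.

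Discussion, Relevance, adds that "we will determine general parameters that are necessary to make a telemedicine postoperative follow-up program more cost-effective". No interaction or subgroup analysis of net benefit is described.

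**The concern.** Cost-effectiveness is a comparison of arms. A variable predicts it only if the arm difference in net benefit changes with that variable. In the printed model that difference is one constant, so none of the listed variables can show such a change, whatever the data contain. The use announced under Measuring Predictor Variables therefore cannot be met by the model under Net Benefit Regression.

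Distance is where this matters most. Travel to specialised care is the reason given for the app, and a reader who takes the covariates as predictors will look at B3. Under the protocol's own costing B3 should be negative, which looks as if distance counts against the app, although the app's advantage should grow with distance.

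**Working it through.** **Inputs**

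- Model and role of B1: Net Benefit Regression.
- Visits per patient: v_c = 2 in person; v_i = 1 with the app if exactly one is averted (Sample Size).
- Travel cost proportional to km (Secondary Outcomes). Let t be travel cost per km of one-way distance per clinic visit. The protocol gives no value for t.
- Software: CAD 3.50 per patient per day (Secondary Outcomes).
- Patients: 32 per group analysed; 32/0.9 = 35.6, so 36 per group, as stated.

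The protocol prints no numerical result for this model, so there is nothing further to reproduce.

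**Step 1. What the printed model allows.** INB(x) = nb(TX=1, x) - nb(TX=0, x) = B1. Its derivative with respect to km, age or any other covariate is 0 by construction.

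**Step 2. What the costing implies for distance.** If complications are unrelated to distance, net benefit falls by t x v_c per km in the in-person arm and by t x v_i per km in the app arm. Randomisation is 1:1, so arm is unrelated to km and the common slope is the average of the two:

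- B3 = -t(v_c + v_i)/2 = -t(2 + 1)/2 = -1.5t
- slope of INB on km = t(v_c - v_i) = t(2 - 1) = +1.0t

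B3 is negative whenever patients travel to any visit. The INB slope is positive whenever the app averts visits.

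**Step 3. Check by simulation.** 1,000 trials of 64 patients per setting, fitting arm and km, without and with TX x km. Assumptions not in the protocol: CAD 0.50 per km each way (t = 2 x 0.50 = 1), CAD 60 other cost per visit, exponential distance with mean 150 km, Poisson visits, residual SD CAD 100, no complication effect. App cost is 3.50 x 30 = CAD 105.

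| Visits, in-person / app | B3: formula | B3: simulated | TX x km: formula | TX x km: simulated | Interaction significant at 5% |
|---|---|---|---|---|---|
| 2 / 1 | -1.50 | -1.52 | +1.00 | +0.99 | 21% |
| 2 / 0.5 | -1.25 | -1.24 | +1.50 | +1.53 | 37% |
| 1 / 0.5 | -0.75 | -0.75 | +0.50 | +0.50 | 13% |
| 1 / 0.05 | -0.525 | -0.52 | +0.95 | +0.95 | 35% |
| 2 / 2 | -2.00 | -2.00 | 0 | -0.07 | 7% |

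At 2 versus 1 visits B3 was negative in 99.9% of trials. The last row shows that B3 carries no information about the app's advantage: it is most negative when the app averts nothing.

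**Step 4. Illustrative size.** With one visit averted and other cost c per visit, INB(km) = t x km + c - 105, in CAD:

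| Assumed t, c | 10 km | 100 km | 300 km |
|---|---|---|---|
| t = 1, c = 100 | 5 | 95 | 295 |
| t = 1, c = 60 | -35 | 55 | 255 |
| t = 0.5, c = 100 | 0 | 45 | 145 |

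The printed model replaces each row by one number. With t = 1, c = 100 and lognormal distance with median 40 km (4,000 trials, 32 per arm), it gave mean B1 = 62 and B3 = -1.51. Since INB = km - 5 here, 62 is the value at a mean distance of about 67 km. It is correct as an average but does not describe near or far patients. Power for TX x km was about 12% in that setting.

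**The case against.** The strongest reply is that the regression does what it is declared to do. Net Benefit Regression sets out to judge the intervention's cost-effectiveness overall, the acceptability curve uses B1 alone, and under 1:1 randomisation B1 estimates the average incremental net benefit with or without interactions. The reasons under Measuring Predictor Variables (effects on wages, travel cost and surgical success) fit adjustment covariates. Nothing says that B3 will be interpreted. Leaving effect modification out of a trial of 64 to 72 patients is defensible.

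Most of this stands. Two stronger readings should be set aside:

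- A reader might infer that B3 would contradict a hypothesis of the trial. No such hypothesis is stated. The nearest text, in Relevance, says that by "eliminating the barriers of distance, telemedicine can improve access to breast reconstruction among breast cancer survivors", which is an access rationale.
- A reader might infer that the analysis fails a formal objective of finding which patients benefit most. The Research Question concerns averted visits. The parameters mentioned in Relevance are not named and may mean programme cost inputs such as software price or training, varied outside the regression.

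The CAD amounts also rest on assumed inputs. Counted visits include family physician and emergency visits, which may be close to home. In the formulas v should then count only visits that require travel to the hospital. This shrinks both slopes but leaves the signs opposite as long as the app averts some of those visits.

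The reply does not remove the mismatch itself. One section calls the covariates predictors of cost-effectiveness, and the equation does not let cost-effectiveness depend on them. Because the equation is printed in full, this is not a detail left open for another document.

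**Conclusion.** The point holds as an inconsistency between the role given to the covariates and the model that is meant to serve it. It is not an error in the overall cost-effectiveness estimate. B1 and the acceptability curve built on it stand, and the primary outcome is untouched.

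At the protocol's visit numbers the distance coefficient is -1.5t and the change in the app's advantage with distance is +1.0t. The opposite signs need only three conditions: travel cost that rises with distance, fewer clinic visits in the app arm, and complications unrelated to distance. The amounts in CAD and the power figures depend on assumed unit costs, distances and variances, and are illustrations only.

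**What to change.** In Net Benefit Regression, add one pre-specified exploratory term, B9(TX x [km - mean km]), and centre km in B3 in the same way. B1 then remains the average incremental net benefit, and the planned acceptability curve can still be drawn from it. B3 becomes the distance slope in the in-person arm. Report B1 + B9(km - mean km) with a 95% CI at a few distances named in advance, as estimates rather than tests.

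In both Measuring Predictor Variables and Net Benefit Regression, state that B2 to B8 are adjustment terms and will not be read as predictors of cost-effectiveness. Separate acceptability curves for near and far patients, or further interactions, are optional.

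The cost is one model term and two sentences, with no new data. The drawback is imprecision: power for the interaction was about 12% to 37% under the assumptions above, so its interval will be wide and should be presented as such.

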### Handling Missing Data

We will generate “best” and “worst” case scenarios for the missing data to determine if there is any change in findings.

## Discussion

### Relevance

At Women’s College Hospital, over 5000 elective ambulatory surgeries are performed each year. These numbers are small compared to other hospitals, such as the nearby Trillium Health Center, where over 20,000 surgeries are performed annually. These numbers will continue to grow as we follow trends in the United States where currently 60-70% of the surgical procedures are performed in the ambulatory setting [28]. Smartphones are becoming ubiquitous throughout Ontario. Using such an ubiquitous technological platform to reduce health care costs for patients and providers in an already large and growing patient population is in concordance with the Ontario Action Plan. Telemedicine is identified as a way to improve access to specialty care among underserviced communities [29]. Breast reconstruction is an underused option for patients, despite its well-known psychosocial benefits in breast cancer patients [2,8]. In fact, Canada underperforms next to countries like England and the United States. Particularly, low income and nonurban residence is associated with decreased rates of breast reconstruction [9]. By reducing costs to society, of which a component represents costs borne by patients, and eliminating the barriers of distance, telemedicine can improve access to breast reconstruction among breast cancer survivors.

Telemedicine literature is often criticized for its lack of rigorous economic evaluation [28]. In assessing the cost-effectiveness of mobile phone follow-up, we will determine general parameters that are necessary to make a telemedicine postoperative follow-up program more cost-effective. Upcoming telemedicine pilot programs can model costs around these general parameters.

### Knowledge Translation Plan

The study findings will yield information relevant to clinicians, hospital administrators, and decision makers regarding support and investment in telemedicine follow-up technology. If the mobile phone app (QoC Health Inc, Toronto) is demonstrated to be cost-effective, this would support its dissemination among other divisions of ambulatory surgery, including orthopedic and general surgery. It will advise policy decision makers and managers at the regional and local level regarding who are responsible for feasibility assessment, resource allocation, program design, and quality improvement. Several knowledge dissemination activities are planned. Dissemination activities will be pursued initially in the Greater Toronto Area, and eventually, nationally to ensure that the research findings reach a broad audience. To enhance knowledge dissemination, a user-friendly report will be produced using the standard 1:3:25 format recommended by the Canadian Health Services Research Foundation (1 page of key messages for decision makers; a 3-page executive summary; and a 25-page final report written in an accessible language).

### Knowledge Translation Among Health Care Providers

Locally, we will submit our findings for presentation at Gallie Day at the University of Toronto. Gallie Day attracts surgeons from all fields at the University of Toronto. Surgeons who attend this event tend to have a hand in either research or hospital administration. They work at various hospitals throughout the Greater Toronto Area. And we will present our findings at the American Society of Plastic Surgery Annual Meeting. This meeting tends to draw as many Canadians as the Canadian Society of Plastic Surgery Annual Meeting, as well as American and international plastic surgeons. This is a suitable population for dissemination as most plastic surgeons perform a large quantity of elective ambulatory surgeries. We will aim for publication in *Canadian Medical Association Journal* or *JAMA Surgery*. These journals attract a breadth of readers that include plastic surgeons and other types of ambulatory surgeons.

### Knowledge Translation Among Administrators and Policy Decision Makers

We will submit our findings for presentation at the Ontario Hospital Association Conference and Health Achieve conference. These conferences tend to attract administrators and policy decision makers. Findings will be further communicated nationally through use of various listservs.

To facilitate the research process and to enhance involvement, 2 or more members of the team meet weekly. Such meetings foster communication and progress. The clinicians (JS and MB) on our team are enthusiastic to improve ease of follow-up with telemedicine. They have indicated that they are ready to champion research results within their respective organizations by narrowing the gap between evidence and action, and they wish to be proponents of evidence-informed decision making for the system and policy environment.

### Limitations

There are three main study limitations. First, the timeline of data collection is limited to the first 30 days postoperatively. This reference was based on literature around the first 30 days postoperative. Studies reveal that the 2-week period after hospital discharge is the most vulnerable time and 75% of complications show up within 14 days of discharge [21]. Complications (eg, capsular contracture) beyond 30 days represent the minority; we will minimize bias by using the same timeline of data collection in both the telemedicine and conventional follow-up group.

A second limitation lies in the potential generalizability of the findings. Study participants will be drawn from those receiving ambulatory breast reconstruction at WCH, and consequently, the findings may not necessarily generalize to patients receiving in-patient breast reconstruction (eg, bilateral deep inferior epigastric perforator [DIEP] flap). However, the populations served are quite diverse in terms of their clinical, demographic, and regional background, which may help to improve generalizability to elective ambulatory surgery patients including the majority of breast reconstruction performed in the community. In addition, because only female English-speaking participants without psychiatric condition or chronic pain syndrome will be recruited, the findings may not be generalizable to certain populations (eg, non-English speaking).

A third limitation surrounds self-reporting and estimating costs. We will rely on in-person follow-up patients to provide us with estimated time of travel from home to clinic and back to home. We will limit bias by correlating this with distance from clinic information based on postal code. We also must rely on average wage estimates from Statistics Canada and average travel costs from Canadian Automobile Association. These estimates are commonly used in cost-effectiveness literature.

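### Correlating self-reported travel time with postal-code distance cannot limit a uniform reporting error, so the time-cost comparison keeps a differential measurement error of unknown direction

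*Protocol article*

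**What the plan says.** The Limitations section of the protocol article names self-report and cost estimation as the third main limitation. On travel time it states: "We will rely on in-person follow-up patients to provide us with estimated time of travel from home to clinic and back to home". The remedy follows at once: "We will limit bias by correlating this with distance from clinic information based on postal code".

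Measuring Outcome Variables, Secondary Outcomes, sets out where each cost element comes from:

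- For clinic visits, the patient's cost survey collects, among other items, "total time commitment of in-person follow-up".
- For the app: "We will determine foregone leisure time based on questionnaire time stamps from software records".
- Travel expense is not self-reported: "We will determine travel costs based on distance from home postal code to WCH".
- The value of an hour is not self-reported either: "We will determine foregone income based on average Ontario wages for a given age and sex of the patient".
- The survey is not confined to one arm: "Both mobile app and conventional follow-up patients at 4 weeks postoperative will complete our cost survey".

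Under Net Benefit Regression, cost means all societal costs over 30 days. The acceptability curve plots the probability that the study-arm coefficient is positive.

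**The concern.** The article identifies a source of bias and says how it will be limited. The method named does not have that property. A correlation shows whether patients who live further away report longer journeys. It does not show whether the journeys reported are too long or too short on average, and the average is what enters the cost. Distance is in kilometres and reported time in minutes, so the two cannot be compared in level until distance is converted to an expected time.

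The two modes of follow-up are also timed by different instruments: patient recall for visits, software logs for the app. If recall is off by a common factor, the error builds up with each visit attended. The arms are expected to differ in visits, so the error passes into the study-arm coefficient. Having distance as a covariate in the regression does not remove it, because that adjusts for where patients live and not for errors in their reported hours. A high correlation could then be read as reassurance that it cannot give.

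**Working it through.** The plan gives no figure on this point to reproduce. The check is of the safeguard's logic, followed by an illustration of size.

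**Step 1. Algebra.** Let D be distance, T true travel time, and R = a + bT reported time, with b > 0. Then

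corr(D, R) = b·Cov(D, T) / [SD(D)·b·SD(T)] = corr(D, T).

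Both a and b drop out. The mean error is a + (b − 1)·mean(T), which the coefficient does not contain.

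**Step 2. Simulation.** All inputs are assumptions except the group size of 36, which is the plan's target per arm. Distance is log-normal with median 40 km and log-scale SD 1. True round-trip time is 30 minutes plus the return journey at 70 km/h, plus normal noise with SD 15 minutes. There were 4,000 runs.

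| Reporting | Correlation with distance | Slope (min/km) | Intercept (min) | Mean error (min per visit) |
|---|---|---|---|---|
| Accurate | 0.990 | 1.71 | 29.9 | 0 |
| +20% | 0.990 | 2.06 | 35.9 | +28.6 |
| +50% | 0.990 | 2.57 | 44.9 | +71.4 |
| Flat +60 min | 0.990 | 1.71 | 89.9 | +60.0 |
| −20% | 0.990 | 1.37 | 23.9 | −28.6 |

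The correlation is the same in every row. The fitted line does move, so the postal-code data could reveal the error if reported time were set against expected time.

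**Step 3. Effect on the time comparison.** The Risks section puts one app response at about 5 minutes. The Abstract implies 14 daily plus 2 weekly reports, or 16. The Intervention section implies 14 plus 4, or 18. App time is therefore 16 × 5 = 80 to 18 × 5 = 90 minutes per patient. The documents give no length for a visit, so 120, 240 and 360 minutes door to door are assumed. Time saved by averting one visit, measured against 90 minutes of app use, is f × visit − 90, where f is the ratio of reported to true time for the whole visit:

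| Visit (min) | f = 0.5 | f = 0.8 | f = 1 (true) | f = 1.2 | f = 1.5 |
|---|---|---|---|---|---|
| 120 | −30 | 6 | 30 | 54 | 90 |
| 240 | 30 | 102 | 150 | 198 | 270 |
| 360 | 90 | 198 | 270 | 342 | 450 |

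For example, at 240 minutes and f = 1.2: 288 − 90 = 198, against a true 150. At f = 0.8: 192 − 90 = 102. The apparent saving moves either way with f.

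**Step 4. What is exposed.** Travel expense comes from postal code and the hourly value from average wages, so only the number of hours is open to this error. The safeguard addresses travel hours alone. The article states no check on reported waiting or clinic time.

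**The case against.** The strongest reply is that correlating may be loose wording for cross-checking each report against distance, with the detail left to a fuller document. Step 2 shows that the same data would support such a check. That stands as a reason to call this a repairable wording and method problem. It does not rescue the safeguard as written, because the article names correlation and claims that it limits bias.

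The article also discloses self-report as a limitation, and software logs are a sensible source for app time. Both are fair, but the point here concerns the claimed mitigation. The contrast is by mode of follow-up and not strictly by arm, since app patients also complete the cost survey and may attend visits. That too stands.

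A reader might go further and infer that the comparison is biased towards the app. The documents do not support this. They speak only of bias, with no direction or size, and under-reporting of visits or idle time within the time stamps would favour in-person care. A reader might also infer that the time stamps miss the photos or a helper's time, or that the cost survey has no question on these. What the logs record is not stated, and Multimedia Appendix 4 is listed by title only, so these remain guesses.

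**Conclusion.** The point holds in this form: the stated safeguard can neither show nor remove a uniform over- or under-statement of travel time. The reported hours therefore enter the societal cost unchecked, with a differential error between the two modes of follow-up whose direction is unknown. The invariance result needs no assumptions. The minutes do: under the assumed distances and speed, a mean error between −28.6 and +71.4 minutes per visit leaves the correlation at 0.990.

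No monetary size can be fixed from the documents. One might take 30% over-reporting of a 1 to 6 hour round trip at $25 per hour, which gives $7.50 to $45, or $15 to $90 with a caregiver at the same rate. Set against the software charge of $3.50 × 30 = $105, that is about 7% to 86%. Everything in that range except the daily charge is assumed, over-reporting included, so it illustrates scale and is not evidence of bias. The charge is also only one of the app cost lines. The primary outcome, the count of physician visits, is untouched.

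**What to change.** Replace the correlation with an agreement check. Convert each home postal code to an expected round-trip time to the hospital, and report the mean and spread of reported minus expected travel time. Then repeat the net benefit regression and the acceptability curve with travel time for every clinic visit in either arm costed from the postal-code route, and state whether the conclusion changes. This works whichever way the error runs.

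The cost is a little extra analysis and an assumed travel mode. A mean difference may partly reflect a wrong speed, so the assumption should be stated and varied. Postal codes are already used for travel expense and patients are already to be asked for travel time, so no new data are needed. Reported waiting and clinic time would remain unchecked, and the limitations text should say so. Replacing it with booked clinic times in the main analysis is not advised, since a schedule can miss real waiting.
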